#### Mental health-related measures

The *Perseverative Thinking Questionnaire* (PTQ) is used to measure repetitive negative thinking [57]. The PTQ is a 15-item self-report questionnaire, comprising statements about 3 processes: core features (repetitive, intrusive and difficult to disengage thoughts), unproductiveness and capturing mental capacity. Each item is rated on a 5-point Likert scale, resulting in a global repetitive negative thinking score ranging from 0 to 60. Higher scores indicate more perseverative thinking. The Dutch version of the questionnaire has been shown to have excellent reliability (Cronbach’s *α* = 0.94) [58].

The *Five Facet Mindfulness Questionnaire-Short Form* (FFMQ-SF) is used to measure mindfulness skills [59]. The FFMQ-SF consists of 24 items divided into 5 facets: observing, describing, acting with awareness, non-judging and non-reactivity. Each item has 5 answer options, and higher scores indicate more mindfulness skills. All facets of the Dutch version in a sample with depressive symptomatology has been shown to be reliable (Cronbach’s *α* = 0.73–0.91) [60].

The 12-item *Self-Compassion Scale–Short Form* (SCS–SF) consist of 6 scales to measure self-compassion: self-kindness, self-judgment, common humanity, isolation, mindfulness and over-identification [61]. Each scale consists of 2 items, using a 7-point Likert scale. A total self-compassion score is computed by reversing the negative subscale items (self-judgment, isolation, over-identification) and then combining the subscale scores. Higher scores indicate more self-compassion. The psychometric properties of the Dutch SCS-SF have been shown to be good (Cronbach’s *α* = 0.87) [61].

The *Mental Health Continuum-Short Form* (MHC-SF) is a 14-item self-report questionnaire that measures 3 dimensions of positive mental health: emotional well-being, psychological well-being and social well-being [62]. Items are scored on a 6-point Likert scale. All items are summed and higher scores indicate greater levels of positive mental health. The internal consistency of the total score of the Dutch version of this questionnaire has been shown to be very good (Cronbach’s *α* = 0.89) [63].

The *Mindfulness Adherence Questionnaire* (MAQ) is a 12-item questionnaire about mindfulness practice [64]. The first 2 items measure formal practice in terms of frequency and average duration of practice. The remaining items measure the quality of formal practice. Items are scored on a 7-point Likert-scale. Higher subscale scores reflect higher practice quality for that respective practice type. Because a Dutch version of the questionnaire was not available yet, we translated and back-translated the original MAQ for the purpose of this study. The reliability of the English version has been shown to be adequate (Cronbach’s *α* = 0.79) [64].

#### Cost-effectiveness

Cost-effectiveness is investigated using the *Trimbos and iMTA questionnaire for Costs associated with Psychiatric illness* (TiC-P) as a reliable and valid measure of healthcare utilization and productivity losses at work and in daily life [65, 66]. Unit cost estimates will be derived from the national manual for cost prices in the healthcare sector [67].

Health-related QoL, using the *EuroQol-5D-5L* (EQ-5D), is used to assess quality adjusted life years [68]. The EQ-5D consist of 5 dimensions: mobility, self-care, usual activities, pain/discomfort and anxiety/depression. Each dimension has 5 levels: no problems, slight problems, moderate problems, severe problems and extreme problems. The EQ-5D index is calculated by applying predetermined weights to the 5 dimensions, and gives a societal-based global ‘utility score’ of the participant’s health status on a scale between − 0.33 (worse than death) and 1 (perfect health). Based on these utility scores at T0 and T1, Quality-Adjusted Life Years (QALYs) were calculated for each participant with the Area Under the Curve method: ((EQ-5D T0 + EQ-5D T1)/2)*(3/12) and using the Dutch index tariff [69]. This questionnaire has been validated in IBD patients [70].

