## Methods

### Study design

The MindIBD trial is a prospective, multicentre, parallel-group RCT comparing MBCT plus treatment as usual (TAU) versus TAU alone. Assessments are conducted at baseline (T0) and at 3 (T1), 6 (T2), 9 (T3) and 12 (T4) months follow-up. To evaluate the feasibility for implementing MBCT in the care for patients with IBD, a process evaluation with qualitative interviews will be part of the project. The study protocol has been approved by the ethical review board CMO Arnhem-Nijmegen (#2021–7319; NL75762.091.20).

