#### Cost-effectiveness

The cost-effectiveness evaluation will be carried out from both a healthcare and societal perspective considering direct as well as indirect costs. Data on resource use (healthcare uptake) and productivity losses will be collected with the TiC-P. Total costs, measured with the TiC-P will be estimated using an incremental bottom-up micro-costing approach, where costs for each patient will be obtained by multiplying information on each element of service with standard costs, based on the Dutch guideline for costing research [67]. We will consider three types of costs: (1) intervention costs of offering MBCT; (2) costs related to healthcare uptake; and (3) costs stemming from productivity losses due to absenteeism. The recall period will be four weeks at baseline, and will consist of three months (the entire period between each follow-up assessment) at 3, 6, 9 and 12 months follow-up. Health related QoL data (based on EQ-5D) from baseline up till 12 months will be used to calculate QALYs using the trapezium rule. Overall mean and median costs and health related QoL will be compared across the conditions and where relevant, differences will be calculated inclusive of 95% confidence intervals. Incremental cost-effectiveness will be determined in terms of incremental costs per QALY gained. The Incremental cost-effectiveness ratio will be determined on the basis of incremental costs and effects of MBCT compared to TAU. Bootstrap simulations with 1.000 replications will be used to get uncertainty intervals in our economic evaluation, taking into account the correlations between costs and QALYs. In addition, a cost-effectiveness acceptability curve will be produced to show the probabilities that given a certain value for the cost-effectiveness threshold, either of the tested strategies is the cost-effective option. In case of missing data, we will use multiple imputation methods to estimate the missing values.

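### QALYs are defined in two incompatible ways: over three months from T0 and T1 in the outcome section, and over 12 months in the analysis section

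*Protocol article*

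**What the plan says.** The outcome section (Outcome measures, Cost-effectiveness) introduces the EQ-5D-5L and then states how QALYs are obtained: "Based on these utility scores at T0 and T1, Quality-Adjusted Life Years (QALYs) were calculated for each participant". The formula follows: "Area Under the Curve method: ((EQ-5D T0 + EQ-5D T1)/2)*(3/12"). It uses two time points and a weight of a quarter of a year.

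The analysis section (Statistical analysis, Cost-effectiveness) says: "Health related QoL data (based on EQ-5D) from baseline up till 12 months will be used to calculate QALYs using the trapezium rule". The result it feeds is also fixed there: "Incremental cost-effectiveness will be determined in terms of incremental costs per QALY gained".

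The data collection covers the whole year. Under Study design: "Assessments are conducted at baseline (T0) and at 3 (T1), 6 (T2), 9 (T3) and 12 (T4) months follow-up". Table 1 ticks both the EQ-5D and the TiC-P at all five. After baseline, the cost recall period "will consist of three months (the entire period between each follow-up assessment) at 3, 6, 9 and 12 months follow-up", so the four recall periods together cover 12 months.

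**The concern.** The two sections describe the same quantity and cannot both be followed. The outcome section does not call its formula an example, a first segment or an additional short-term analysis; it presents it as the way each participant's QALYs are obtained. The analysis section describes one economic evaluation with one incremental ratio and mentions no three-month version.

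The incremental cost per QALY, its bootstrap intervals and the acceptability curve all depend on which rule is used. Cost-effectiveness is a stated aim, and the Discussion links implementation in practice to MBCT proving cost-effective. Two live definitions also leave the horizon open to choice once results are known.

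The specific risk is that an analyst copies the explicit formula, because it is the only one printed, and sets it against costs gathered over 12 months. The effect side would then cover a quarter of the period of the cost side.

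**Working it through.** **Inputs**
- Rule A (Outcome measures, Cost-effectiveness): T0 and T1 only, weight 3/12 = 0.25 year.
- Rule B (Statistical analysis, Cost-effectiveness): baseline to 12 months, trapezium rule.
- Assessment grid (Study design; Table 1): 0, 3, 6, 9 and 12 months.
- Cost period (Statistical analysis, Cost-effectiveness): four recall periods of three months, 4 × 3 = 12 months.
- Utility difference between arms and its time course: not given. Everything from step 3 on is therefore an assumption, shown as a range.

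**1. The two rules in full.** Write U0 to U4 for the utilities at T0 to T4.
- A: 0.25 × (U0+U1)/2.
- B: 0.25 × [(U0+U1)/2 + (U1+U2)/2 + (U2+U3)/2 + (U3+U4)/2] = 0.25 × (U0/2 + U1 + U2 + U3 + U4/2).

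A is exactly the first of the four segments of B.

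**2. Facts that need no assumption about the treatment effect.** With utility 1 throughout, A gives 0.25 × 1 = 0.25 QALY and B gives 0.25 × 4 = 1.00 QALY. A omits three of the five measurements (T2, T3, T4).

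**3. Gain between arms.** Let Δ0 to Δ4 be the mean utility differences (MBCT + TAU minus TAU), with Δ0 = 0 (equal baseline).
- Gain under A = 0.25 × Δ1/2 = 0.125 Δ1.
- Gain under B = 0.25 × (Δ1 + Δ2 + Δ3 + Δ4/2).

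For a fixed positive incremental cost over 12 months, the cost per QALY under A exceeds that under B by the factor (gain under B)/(gain under A).

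**4. Range over assumed courses.** In all rows but the last, d is the difference at T1; in the last row, d is the difference reached at 12 months.

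| Assumed course | Δ1, Δ2, Δ3, Δ4 | Gain A | Gain B | Factor |
|---|---|---|---|---|
| Present at T1 only | d, 0, 0, 0 | 0.125d | 0.25d | 2 |
| Half at T2, zero from T3 | d, d/2, 0, 0 | 0.125d | 0.375d | 3 |
| Linear fade to zero at 12 months | d, 2d/3, d/3, 0 | 0.125d | 0.5d | 4 |
| Linear decline, half retained at 12 months | d, 5d/6, 4d/6, d/2 | 0.125d | 0.6875d | 5.5 |
| Sustained from T1 | d, d, d, d | 0.125d | 0.875d | 7 |
| Doubling after T1 | d, 2d, 2d, 2d | 0.125d | 1.5d | 12 |
| Linear growth over 12 months | d/4, d/2, 3d/4, d | 0.03125d | 0.5d | 16 |

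Illustration for the sustained course with an assumed d = 0.05: A gives 0.125 × 0.05 = 0.00625 QALY and B gives 0.875 × 0.05 = 0.04375 QALY; 0.04375/0.00625 = 7.

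**5. Lower limit.** If Δ1 is positive and none of Δ2 to Δ4 is negative, the gain under B is at least 0.25 Δ1, which is twice 0.125 Δ1. The factor then cannot be below 2. It falls below 2 only if the difference reverses after T1.

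**The case against.** The best defence is that the plan already contains the right rule where it counts. The analysis section fixes the 12-month horizon, the trapezium rule, cost recall over the same year and the incremental ratio. Table 1 schedules both instruments at every assessment. The outcome section mainly describes the instrument, and its formula is just the first segment of the 12-month calculation. Its past tense, in a trial whose last follow-up was still to come according to Trial status, is consistent with leftover text; that is an inference, not something the article says. On this view the conflict is a slip that a careful analyst would settle in favour of 12 months.

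Much of this stands. It lowers the severity and shows which way the conflict should be resolved. It does not remove the conflict: the only QALY formula printed is the three-month one, and it is not marked as partial or secondary. Nor is this a detail that an article may leave to a fuller document, because the article states both rules.

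A reader might infer two stronger things, and the documents support neither.
- *That the plan sets three-month QALYs against 12-month costs.* No section does so. The outcome section's formula comes with no cost horizon, and the analysis section takes both utilities and costs over 12 months. The mismatch is a risk that arises only if the formula of one section is combined with the costs of the other. If the formula were used with costs for months 0 to 3, the numerator would change too, and the factors above would not apply to the cost per QALY.
- *That the QALY gain would be cut about sevenfold.* Seven holds only for equal baseline utility and a T1 difference sustained unchanged to T4. The article states neither, and other plausible courses give from 2 to 16.

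**Conclusion.** The contradiction is real: two incompatible QALY definitions, one capped at 0.25 and one at 1.00, with no text to rank them. The outcome section's formula is wrong as written when read against the analysis section and the assessment schedule.

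The consequence is conditional. Used with the 12-month costs, the three-month formula would understate the QALY gain and inflate the cost per QALY. Under equal baseline utility and a positive incremental cost, the factor is 2 for a difference at T1 only, 4 for a linear fade to zero, 7 for a sustained difference and 16 for linear growth. No single factor can be taken from the documents.

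The point is an internal inconsistency confined to the economic evaluation. The primary HADS analysis, the sample size and the clinical secondary outcomes do not depend on it, and no data are lost. It should be fixed, but it does not threaten the trial's main conclusion.

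**What to change.** In Outcome measures, Cost-effectiveness, replace the two-point formula with the five-point trapezium that the analysis section implies:

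QALY = 0.25 × [(U0+U1)/2 + (U1+U2)/2 + (U2+U3)/2 + (U3+U4)/2]

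State in both cost-effectiveness sections that 12 months is the common horizon for costs and QALYs. If a three-month analysis is also wanted, label it secondary and pair it with the costs of months 0 to 3. Since the course itself lasts eight weeks, its costs fall early, so such an analysis carries them while leaving out any later benefit; it should be read with that in mind.

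The cost is one formula and one sentence. All EQ-5D and TiC-P assessments needed are already scheduled. The correction should be dated and made before the economic data are analysed by arm.

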#### Qualitative interviews

In addition to the questionnaires, a qualitative study is embedded in the project, including a subsample of the trial participants and other stakeholders (e.g. gastroenterologists, mindfulness teachers, health insurance companies, healthcare managers) for in-depth interviews with regard to (a) the usefulness of MBCT in coping with their illness and improving self-care, and (b) the feasibility of MBCT, including possible barriers and facilitators for implementation. Trial participants will be purposively sampled (e.g. disease type, age, sex, compliance with MBCT), including as much diversity in perspectives as possible. We will continue to invite participants until saturation of the data has been reached, i.e. when no new themes are coming up any longer.

### Data management and monitoring

Data will be collected using CastorEDC [26]. Unique participant codes will be assigned to ensure confidentiality. Data that lead to contact details of the participants will be stored in a separate dataset from all other research data collected during the study. Access to the code that couples the study data to the contact details is limited to the principal investigator and a restricted number of researchers. All data will be stored using encrypted digital files and password protected folders with access to a limited number of researchers. The data will be securely stored according to the Personal Data Protection Act for a minimum period of 15 years after the study is completed. During the trial, access to the data will be limited to the researchers. Once trial results are reported, anonymised data will be made available upon reasonable request.

With regard to NFU-classification, the risk of harm in this study is negligible. Therefore a data monitoring committee has been deemed unnecessary for this study. For the same reason, no interim analysis is planned.

### Safety monitoring

In accordance with Good Clinical Practice guidelines, (serious) adverse events ((S)AEs) are reported. Adverse events that may occur are examined at each assessment by explicitly asking participants if they have experienced any adverse events. Although the occurrence of temporary difficulties is not uncommon [71], serious or long lasting effects are expected to be minimal [72]. IBD flares are not classified as adverse events, because these are expected in this specific population [2].

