## Background

Inflammatory Bowel Disease (IBD), mainly consisting of Crohn’s disease and ulcerative colitis, is characterised by chronic relapsing inflammation of the intestinal tract. In the Netherlands, currently about 90,000 patients have been diagnosed with IBD and the prevalence seems to be rising worldwide [1]. The disease manifests mainly in young adults, aged between 15 and 30 years, who are in a turbulent part of their life, finding their way with housing, friends, education and perhaps starting a family and career. Physical symptoms include abdominal pain, diarrhoea, rectal bleeding and fatigue. Although the arsenal of drugs has increased in past decades, there is no cure for the disease and patients are usually treated with different (immunosuppressive) medications for a long time. Despite these treatment options, flares are common with cumulative rates of 69–93% after 5 years for patients with Crohn’s disease and 78–82% for patients with ulcerative colitis [2].

Besides physical symptoms, many IBD patients experience psychological distress, including symptoms of depression and anxiety. This could be due to its unpredictable course and prognosis, difficulties accepting their chronic disease and side effects of medication [3]. About a quarter of patients in remission experience depressive symptoms and about a third experience symptoms of anxiety, which is two to three times higher than healthy controls [4]. These numbers nearly double during flares [3, 4]. Psychological distress has been associated with a decrease in self-care and quality of life (QoL) and an increase in the experience of physical symptoms, including fatigue. Besides that, these patients are more likely to seek medical care, which leads to higher healthcare costs [3]. Moreover, the association between psychological distress and disease activity might be bidirectional, since it has been suggested that perceived psychological distress may affect the onset and course of IBD [5]. However evidence is scarce and inconsistent [5, 6].

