### Procedure and assessments

Figure 1 provides a flowchart of the study procedure. In order to minimize the risk of selection bias by attending physicians, all IBD patients treated in these hospitals receive an invitation leaflet. Those interested in participation are referred to an online, anonymous pre-screening survey [25], which includes the HADS and questions about the main eligibility criteria. Probably eligible participants are guided to a registration form, after which they receive additional information about the trial and are invited for a research interview. During this research interview the study is explained in more detail, the inclusion and exclusion criteria are reviewed thoroughly and written informed consent is obtained (Appendix 1). Definite eligibility is determined after laboratory screening to rule out anaemia or elevated faecal calprotectin levels. After definite inclusion in the study, participants are invited for the baseline assessment, which consists of: (1) self-report questionnaires; (2) an interview in which demographic and disease characteristics are examined (age, sex, country of origin, level of education, marital status, employment status, body mass index, IBD type, medication use, age at onset of IBD, time since last flare, hospitalizations due to flare, comorbid psychiatric diagnoses); and (3) sleep analysis, using sleep electroencephalography (EEG) headband for three consecutive nights. From baseline until post-treatment, participants are asked to wear an actigraphy wristband for additional sleep data. At post-treatment, they are asked to sleep another three nights with the EEG headband. The post-treatment assessment (3 months after baseline) and the follow-up assessments (6, 9 and 12 months after baseline) consist of self-report questionnaires and an interview by clinician. The 6- and 12-month assessments include blood and stool samples for all participants. The 3- and 9-month assessment includes blood and stool samples only for patients with a suspected flare. Table 1 provides an overview of assessments and measures. The content of the outcome measures is explained below under the heading ‘outcome measures’.

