#### IBD-related measures

The *Short Inflammatory Bowel Disease Questionnaire (SIBDQ)* is used to measure IBD-related QoL [48]. The SIBDQ has 10 items scored on a 7-point Likert scale, grouped into bowel symptoms, systemic symptoms, emotional function and social function. Overall scores range from 10 to 70, with higher scores reflecting better QoL. The SIBQ has been shown to be reliable (Cronbach’s *α* = 0.78) [49].

The *IBD-Control* is used to measure disease control from the patient’s perspective [50]. The IBD-Control questionnaire consists of 13 items and a visual analogue scale, ranging 0-100 (0 = worst control). The 13 items have 3 answer options and include questions about energy, sleep, mood, freedom of discomfort, ability to perform daily activities and treatment concerns. Overall scores ranges from 0 to 26, where lower scores indicates poorer control. The psychometric properties of the IBD-control have been shown to be good (Cronbach’s *α* = 0.85) [50], including the shortened IBD-control-8 version in a Dutch population (Cronbach’s *α* = 0.82) [51].

Clinical disease activity is assessed by clinician-based questionnaires: *Harvey-Bradshaw Index* (HBI) for Crohn’s disease and *Simple Clinical Colitis Activity Index* (SCCAI) for ulcerative colitis [52, 53]. HBI consist of 12 questions about general well-being (score 0–4), abdominal pain (score 0–3), soft stools (1 point per soft stool), abdominal mass (score 0–3) and extra-intestinal manifestations (score 0–1 per manifestation, 8 in total). A flare may be suspected at a score of 5 or higher. SSCAI consist of 9 questions about general well-being (score 0–4), bowel frequency (score 0–2), urgency (score 0–3), rectal blood loss (score 0–3) and extra-intestinal manifestations (score 0–1 per manifestation, 4 in total). In case of a score of 3 or higher, it may indicate a flare.

*Time to flare* is assessed based on the clinical interviews. If a participant reports that they have (had) a flare, the medical record will be tracked. The assessment of the attending physician is leading. A flare is defined by elevated faecal calprotectin levels (> 250 mcg/g) which is validated by a clinical interview plus commencement of any new IBD medication or altered dosing of existing IBD medication. We consider the date of elevated faecal calprotectin levels or change in IBD medication as the start of the flare.

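### IBD flares are excluded from adverse events because they are expected, with no exception for serious ones, so serious flares are neither identified as SAEs nor compared by arm

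*Protocol article*

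**What the plan says.** Under Safety monitoring, the protocol article states "In accordance with Good Clinical Practice guidelines, (serious) adverse events ((S)AEs) are reported". Events are elicited at each assessment by "explicitly asking participants if they have experienced any adverse events". The section then makes one exclusion: "IBD flares are not classified as adverse events, because these are expected in this specific population [2". The exclusion covers flares of any severity.

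Flares are handled as an outcome instead. Under IBD-related measures, "If a participant reports that they have (had) a flare, the medical record will be tracked", and the attending physician's judgement takes precedence. The definition there requires faecal calprotectin above 250 mcg/g, "validated by a clinical interview plus commencement of any new IBD medication or altered dosing of existing IBD medication". Treatment effects at follow-up plans a Cox regression of time to flare over 12 months, MBCT plus TAU against TAU.

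Admission for a flare is named once, under Procedure and assessments, in the list of baseline characteristics: "time since last flare, hospitalizations due to flare, comorbid psychiatric diagnoses". The Background describes how common flares are: "flares are common with cumulative rates of 69–93% after 5 years for patients with Crohn’s disease and 78–82% for patients with ulcerative colitis".

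**The concern.** Whether an event is expected affects how it is reported. It does not settle whether a medical worsening is an adverse event, or whether it is serious. The protocol uses expectedness for that second purpose, in the same section that commits to (S)AE reporting under Good Clinical Practice. An event that is not an adverse event cannot be a serious one, so the rule, followed literally, keeps a flare that leads to admission out of the SAE record.

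This matters here because the trial treats the effect of MBCT on flares as an open question. The Background raises a possible influence of distress on the course of IBD and calls the evidence scarce and inconsistent. Treatment effects at follow-up sets out to examine recurrence. If the direction of effect is unknown, the harms data should be able to show a difference between arms in serious flares. Under this rule they cannot, and a report of few or no SAEs could be literally correct yet incomplete. The trial has no data monitoring committee (Data management and monitoring), so (S)AE reporting is the only dedicated safety channel that the article describes.

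**Working it through.** The point concerns a reporting rule. The plan gives no figure to reproduce, so the main check sets the sections side by side.

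**1. Is there an exception for seriousness?** Safety monitoring gives a general rule to report (S)AEs and one exclusion, for flares. The exclusion has no qualifier.

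**2. Do other data collected after baseline separate serious from non-serious flares by arm?**

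| Source | What it gives | Seriousness identified? |
|---|---|---|
| Time to flare (IBD-related measures; Treatment effects at follow-up) | Date of flare, compared by Cox regression | No: the definition needs raised calprotectin "plus commencement of any new IBD medication or altered dosing of existing IBD medication", with no admission or severity element |
| HBI/SCCAI and laboratory results (secondary outcomes) | Disease activity by arm | No: symptom scores and laboratory values |
| Hospitalisation due to flare (Procedure and assessments) | Baseline history | No follow-up counterpart is named |
| TiC-P (Cost-effectiveness) | Healthcare use over each three-month interval | Collected for costing; no safety use is stated |

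A flare managed with a dose change and a flare leading to admission therefore count alike in the between-arm analysis. No row supplies a by-arm comparison of serious flares.

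**3. Scale of flares as a whole (illustration only).** The inputs are the 5-year cumulative rates in the Background, the target of 136 participants (Sample size calculation) and 12 months of follow-up (Study design). With a constant hazard, the 12-month risk is 1 − (1 − p)^(1/5):

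- Crohn's disease, lower: 1 − 0.31^(1/5) = 0.209; × 136 = 28.4
- Crohn's disease, upper: 1 − 0.07^(1/5) = 0.412; × 136 = 56.1
- Ulcerative colitis, lower: 1 − 0.22^(1/5) = 0.261; × 136 = 35.5
- Ulcerative colitis, upper: 1 − 0.18^(1/5) = 0.290; × 136 = 39.5

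This gives a risk of roughly 21–41%, or about 28 to 56 participants with a flare across both arms. Each end applies a single rate to all 136 participants, so the true mix of disease types would fall between them. The calculation ignores dropout, although the plan allows for 28%. It also ignores that participants enter after at least three months in remission.

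**4. Serious flares.** The documents give no share of flares that are serious, so no count of missing SAEs follows from them.

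**The case against.** The strongest reply is that flares are not lost. They are asked about at every follow-up interview, checked in the medical record when reported, and compared by arm through Cox regression. HBI/SCCAI and laboratory results are compared too, and Comparator: treatment as usual says that all healthcare use is registered. Recording an anticipated disease event as an outcome and not as an adverse event is a recognised choice that avoids double counting. This stands for flares in general. It does not reach serious flares, which none of these sources separates by arm.

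A second reply is that the article condenses a full protocol (version 5, Trial status), which may contain an exception for seriousness. That is possible, and for this reason a reader should not infer that serious flares can in no circumstances have been reported as SAEs. But the article states an affirmative rule with a reason. If the full protocol differs, the sentence misdescribes it and needs correcting anyway.

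Two further inferences are tempting and unsupported:

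- **That serious flares are the most probable serious event in this trial.** The article cites rates for flares of any severity and none for admissions or surgery. The baseline history item says nothing about frequency during the study.
- **That an admission could escape both the SAE record and the flare outcome, for want of a calprotectin sample or drug change.** This uses *flare* loosely for the exclusion and strictly for the outcome. An event that does not meet the protocol's definition is not clearly excluded as a flare, so the general (S)AE rule would apply. The precedence given to the attending physician's assessment, and the extra samples taken when a flare is suspected, also count against it.

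**Conclusion.** The point holds in a limited form. The exclusion is unqualified, its stated reason does not support it, and it sits uneasily beside the (S)AE commitment in the same section. As written, flares meeting a seriousness criterion are not identified as SAEs, and they are compared by arm only within an undifferentiated time to flare. A safety statement about MBCT built on the SAE data would leave them out. What is missing is a seriousness classification and its tabulation by arm. The comparison of flares overall is intact, and the primary HADS analysis is unaffected.

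The number of events concerned is unknown. The 21–41% figure shows only that flares of any kind are likely to be frequent enough for the rule to matter; it rests on the constant-hazard and no-dropout assumptions above. The conclusion depends on the wording of the rule and not on that figure. It would change only if the full protocol already provides for serious flares, in which case the article's sentence alone needs amending.

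**What to change.** Reconcile Safety monitoring, the time-to-flare text under IBD-related measures, and Treatment effects at follow-up as follows:

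- Limit the exclusion to non-serious flares, which stay recorded through the time-to-flare outcome.
- Record any flare that meets a standard seriousness criterion, such as hospitalisation, as an SAE.
- Tabulate all flares and serious flares by arm alongside the other harms.

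Recruitment closed in September 2022 and the last follow-up was due in September 2023 (Trial status), so much of this will be retrospective. For participants already in follow-up, classify flares for seriousness from the interviews and from the medical records already consulted for reported flares, and say in the report that this was done retrospectively.

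The cost is a short amendment, a few more SAE records and a small amount of retrospective classification. No new assessments are needed.
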